# Multicentre, randomised controlled feasibility study to compare a 10-week physiotherapy programme using an interactive exercise training device to improve walking and balance, to usual care of children with cerebral palsy aged 4–18 years: the ACCEPT study protocol

**DOI:** 10.1136/bmjopen-2021-058916

**Published:** 2022-05-30

**Keywords:** Paediatric neurology, REHABILITATION MEDICINE, Developmental neurology & neurodisability

## Abstract

**Introduction:**

Children with cerebral palsy (CP) frequently undertake physiotherapy programmes to improve walking and balance. They often require adult support to exercise in a functional position. A novel interactive exercise trainer has been devised to enable children to exercise with against resistance in a functional position, but its efficacy has yet to be proved. A novel protocol has been developed to determine whether a randomised controlled trial (RCT) is feasible.

**Aim:**

To establish whether it is feasible to conduct an RCT to assess the effectiveness of a 10-week physiotherapy intervention using an interactive trainer in children with CP.

**Methods and analysis:**

This study is multicentre randomised controlled feasibility trial with an embedded qualitative study. Forty children with CP, Gross Motor Function Classification System (GMFCS) I–III will be recruited from community paediatric physiotherapy caseloads. Participants will be randomised to 10 weeks of training with the interactive training device or to usual physiotherapy care. The mediolateral motion of the centre of mass estimate and Paediatric Balance Scale will be explored as potential primary outcomes measures, tested at baseline, 10 weeks and follow-up at 20 weeks. The views of child participants, their parents and physiotherapists will be gained through e-diaries and qualitative interviews.

Feasibility will be determined by examining recruitment and retention rates, completeness of, adherence to the intervention, appropriateness of outcome measures and effectiveness of blinding. Results will be reported in accordance to Consolidated Standards of Reporting Trials (CONSORT) guidelines.

**Ethics and dissemination:**

Physiotherapists, children and parents have informed trial design and information leaflets. Results will be disseminated via publications, conferences and to families. This study has approval from North of Scotland Research Ethics Committee (20/NS/0018).

**Trial registration number:**

ISRCTN80878394.

Strengths and limitations of this studyWe use a mixed-methods approach to assess the feasibility of a proposed randomised controlled trial.This protocol tests the feasibility of two potential primary outcome measures.This study is not designed to determine differences in outcome measurements.

## Introduction

Cerebral palsy (CP) is a group of permanent disorders affecting the development of movement and posture that occurs in 2.1 per 1000 children worldwide.^1^ Difficulties with walking and balance are common and can limit participation in schooling and functional activities.^2–5^ There are multiple causes of walking difficulties in children with CP, including spasticity and weakness, which affects 80% of children.^6^ Additionally, children with CP often have poor balance, which further impacts on everyday functional tasks, such as dressing.^7^

Walking ability can be classified using the Gross Motor Function Classification system (GMFCS).^8^ Children with GMFCS I–III are the focus of the proposed study. Children with GMFCS classification I–II are able to walk functionally outdoors, while children with grade III GMFCS require walking aids.

Physiotherapists frequently prescribe exercise programmes for children with CP aimed at maintaining range of movement, strengthening weak muscles and developing balance skills. In many cases, the children find it hard to undertake exercises in functional positions such as standing, without support from an adult. The Happy Rehab (Innovaid, Denmark) interactive exercise trainer was developed (see figure 1) to help children exercise more independently in a functional supported standing position. It provides support around the hips and additional assistance and resistance via motors aligned to the ankle and knees. This allows the child to exercise muscles functionally in novel ranges, for example, strengthening the thigh muscles with the hip and knee in a straighter position. The games-based exercises may increase motivation and require the child to control the games by moving their weight side-to-side, forward and backward. It is proposed that this may improve balance during dynamic tasks such as walking.

**Figure 1 F1:**
[figure not shown]
The Happy Rehab interactive exercise gaming device. Permission obtained from Innovaid.

A small scale study of the interactive trainer found marked improvements in walking, but had a number of limitations in terms of outcome measures used, lack of follow-up and control group.^9^ Therefore, evidence is still required to establish the efficacy of the equipment. Initially, a study is required to establish the feasibility of such a trial within a community physiotherapy service.

This study aims to establish whether it is feasible to conduct a randomised controlled trial (RCT) of this complex intervention, and to assess the acceptability of the interactive trainer and the trial protocol to physiotherapists, children and their families.

## Objectives

The objectives of the study are to:

Determine the feasibility of a definitive trial.Determine the acceptability of the intervention.Explore the views of a subgroup of study participants.

The trial objectives will be measured by the outcomes set out in table 1.

**Table 1 T1:** Objectives of the feasibility study

Objective	Outcome
**Focus**	**Methods**
Feasibility of definitive trial	
Acceptability of the trial and intervention	Interviews of staff, parents and children
Can we recruit and retain participants?	No of participants eligible No recruited and randomised, date of recruitment recorded on study database Recruitment source No of withdrawals. No of participants lost to follow-up.
Effectiveness and acceptability of randomisation	Comparison of participant characteristics: severity, distribution of motor impairment, associated impairments at baseline Interviews
Effectiveness of concealment of allocation up to week 10	No of times chief investigator correctly guessed treatment allocation
Concurrence with other surgical and medical interventions	No of operations or procedures that target balance and walking during the intervention and follow-up period.
Change in clinical outcome measures	Change in assessment scores of outcome measures
Assess appropriateness of outcome measures	No and percentage of outcome measures completed at each time point Interviews
Feasibility of Intervention	
Adherence to treatment	Diary data frequency and duration of training
Acceptability of treatment intervention	Incidence of breakdown of equipment No of times participants were unable to access equipment Participant view on acceptability of interventions by interview
Cost of intervention and support needed to use it	Local physiotherapist record of staff time and grade used to support intervention. Travel costs of staff and families. No and cost of repairs
Safety of intervention	No and type of SAE and AE
Acceptability of participation	
Acceptability of participation	Themes identified from interviews/photos

AE, adverse event; SAE, serious adverse event.

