### Intervention

Four devices will be available and situated in special schools, CDCsor the child’s home. The child’s physiotherapist will be trained to set up the device targeting exercises to improve range of movement, contracture and muscle weakness. This may include active-assisted hip, knee or ankle movements within specified ranges of movement or side-to-side and forward and back weight transfer. The treating physiotherapist will personalise the exercise programme based on a standardised assessment, including a discussion with the child and their guardian about their goals and aims of any intervention.

The child will use a pseudonym of their choice to log onto the games, and to maintain confidentiality. Children will play the games within the mid-range of muscle length to begin with so that the games are difficult but achievable. This will aid motivation and adherence. After 5 weeks, the child’s physiotherapist will progress the games by requiring the muscles to work in the inner and outer ranges of movement and/or against increased resistance. Training will build up to 20 min per day, 3 days a week over a 2-week period, with progression to a 30 min programme per day, 3 days a week after 5 weeks. The child will train with supervision from by the child’s therapist, teaching assistant, parent or carer. The children will follow a series of games following a 2 min warm up of continuous passive movement. The interactive trainer records the training session (duration, games performed games outcomes) to provide a description of the parameters of training.

The control group will receive a usual care physiotherapy programme individualised for each child lasting 20–30 min.

Collaborative goal setting combined with an e-diary will allow the children and their parents/carers from both arms of the study to monitor progress over time and record their satisfaction with their exercise programme. The research team will assess fidelity through e-diaries, recording of exercise parameters via the interactive trainer and by observing ten exercise sessions and completing a fidelity checklist, to ensure the intervention follows protocol.

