#### Progression criteria

This is determined in advance of recruitment will include minimum recruitment and retention rates (~70%) and a 90% completion rate of outcome measures. Failure to achieve these will indicate that a full trial is not feasible unless our qualitative study indicates clear means by which the rates may be improved. A recommendation list will be generated to enable refinement of the subsequent RCT protocol.

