### Data collection and management

Trial data collected will be recorded on a paper copy of a trial-specific case report form (CRF) and will be considered source data. The blinded assessor will complete the CRFs for all participants. Completeness of data will be maximised by checking all forms at each assessment to ensure there are no missing items. Automatically generated prompts will be sent by email to encourage the participants to return their diaries, should they fail to do so within 2 weeks of the due date. Double-entered data will be compared for discrepancies using a stored procedure, and discrepant data will be verified using the original paper data forms. Before database lock, a proportion of original paper records will be checked against the database to ensure accuracy of the final dataset.

Confidentiality will be maintained by allocating a participant number to all CRFs and keeping the securely codes stored separately. Audiorecorded interviews will be transcribed and anonymised as soon as practicable. Original recordings will be held securely as an encrypted file on the University of Plymouth server, until completion of the qualitative data analysis process, then deleted.

Data will be collected and stored in accordance with the Data Protection Act 1998/General Data Protection Regulation 2018. Data generated from this trial will be available for inspection on request by the participating research team, University of Plymouth representatives, the REC, local R&D Departments and the regulatory authorities.

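### Adherence in the device arm should be measured from the trainer's own session log, with diaries kept as the measure common to both arms, and its role in the progression recommendation stated in advance

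*Protocol article*

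**What the plan says.** The Objectives section says the trial objectives are measured by the outcomes in Table 1. Under feasibility of the intervention, the entry for adherence to treatment is "Diary data frequency and duration of training". No other source is named in that row.

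The Intervention section describes a second source: "The interactive trainer records the training session (duration, games performed games outcomes) to provide a description of the parameters of training". It also gives these recordings a role in fidelity: "The research team will assess fidelity through e-diaries, recording of exercise parameters via the interactive trainer", together with ten observed sessions. The diary is kept by families: "Collaborative goal setting combined with an e-diary will allow the children and their parents/carers from both arms of the study to monitor progress".

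The section on data collection and management provides for e-mail prompts to participants about their diaries, "should they fail to do so within 2 weeks of the due date".

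On what feasibility means, the abstract lists recruitment, retention and completeness, and then "adherence to the intervention, appropriateness of outcome measures and effectiveness of blinding". The Progression criteria section lists "minimum recruitment and retention rates (~70%) and a 90% completion rate of outcome measures".

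**The concern.** Frequency and duration of training are what the adherence row needs. In the device arm the machine captures both at the time of training, without relying on anyone's memory or on a form being returned. Table 1 nevertheless names only the diary, which has two weaknesses that can be seen in the article.

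- **Incomplete return.** Automatic prompts are planned because some diaries are expected to be late or absent. A session with no diary entry has unknown status: it may have been done or missed.
- **Distance from the session.** Children and parents or carers complete the diary, but a therapist or teaching assistant may supervise the training, and it may take place at school or in clinic. The adult filling in the diary may not have been present. Trial design and setting also promises a comparison of training intensity between settings, and diary error that differs by setting would affect that comparison.

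At stake is the quality of one of the main findings of a feasibility study: whether children actually do the training. A related gap is that adherence is said to count towards feasibility, while the listed progression criteria make no use of it.

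**Working it through.** The article states no adherence figure, so there is nothing to reproduce. The check sets the sections against each other and sizes what the log could add.

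**Planned sessions**
- Frequency and length (Trial design and setting): three times per week for 10 weeks, so 3 × 10 = 30 sessions per child.
- Device arm: 40 participants (Sample size) allocated 1:1 (Randomisation), so about 40 / 2 = 20 children.
- Arm total: 30 × 20 = 600 sessions.

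**Sessions of unknown status under diary-only measurement**

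The article gives no expected diary return, so the rates below are assumptions.

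| Share of diary entries returned (assumed) | Sessions with unknown status |
|---|---|
| 90% | 0.10 × 600 = 60 |
| 70% | 0.30 × 600 = 180 |
| 50% | 0.50 × 600 = 300 |

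A complete device log would cover these sessions, provided that it can be linked to the child.

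**Planned minutes**

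The Intervention section has sessions building up to 20 minutes over two weeks, and moving to 30 minutes after five weeks.
- Weeks 1–2: at most 2 × 3 × 20 = 120 minutes
- Weeks 3–5: 3 × 3 × 20 = 180 minutes
- Weeks 6–10: 5 × 3 × 30 = 450 minutes
- Total: at most 120 + 180 + 450 = 750 minutes

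The build-up has no stated steps and programmes are personalised, so 750 is a ceiling. The 30 sessions are the usable denominator; minutes are better described than turned into a percentage.

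**Do the listed progression criteria respond to device use?**

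They have three inputs: recruitment, retention and completion of outcome measures. None is calculated from training. For example, 70% retention of 40 is 28 children. With an assumed true retention of 85%, P(X ≥ 28), where X ~ Binomial(40, 0.85), is 0.996, and the number of sessions delivered does not enter that formula. This shows only that the listed criteria are silent on adherence.

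**How much 20 children can say about adherence**

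Suppose, purely for illustration, that a child is classed as adherent or not and that 14 of 20 (70%) is the mark. The probability of reaching it is 0.0003, 0.058 or 0.998 if the true adherent share is 30%, 50% or 90%. An observed 14/20 has an exact 95% interval of 46% to 88%. Log-based adherence can therefore separate poor from good uptake, but it cannot locate a threshold precisely.

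**The case against.** The strongest reply is that the article already guards against unseen low use. Device recordings feed the fidelity assessment. The Statistical analysis plan section commits to reporting intervention completion with confidence intervals. The qualitative analysis and data synthesis section brings all quantitative and qualitative results together to judge whether the protocol suits the main trial. The diary is also the only named session-level source that both arms share, and the prompts are a safeguard for it. All of this stands. What remains is that none of these passages makes the log the adherence measure or says how adherence bears on progression.

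Three stronger readings are tempting, and the documents do not support them.

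- **A reader might infer that progression would be recommended with the device barely used.** The Progression criteria section says that failing the criteria points to a trial that is not feasible. It does not say that meeting them is enough. It also says the criteria will include the listed items, so the list need not be complete.
- **A reader might infer that diaries overstate adherence.** That is plausible, but nothing in the article shows the direction of diary error.
- **A reader might treat 750 minutes as an exact denominator.** The unspecified build-up makes it an upper limit.

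Nor is it a contradiction for the abstract to name adherence without a cut-off. Effectiveness of blinding is named there too and has no threshold either.

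**Conclusion.** The point holds as an improvement to a stated method. Table 1 rests adherence on self-report in an arm where the trainer already records session duration, and late or missing diaries are foreseen. The information at risk is the status of some of about 600 planned sessions. The count depends wholly on diary return: 60 to 300 over an assumed range of 90% to 50%.

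The second part is narrower. Adherence is named as bearing on feasibility, the listed criteria do not depend on it, and its part in the recommendation is not described. Low use would probably still be noticed through fidelity monitoring and the final synthesis, so this is a matter of stating the role in advance, not of a rule shown to give a wrong answer.

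The conclusion assumes that logs can be exported per child, and that 30 sessions is the intended schedule for every child in the device arm.

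**What to change.** 1. In Table 1 and the SAP, define device-arm adherence as logged sessions out of the 30 planned, over all children randomised to that arm; a child who never starts counts as zero. Describe logged minutes alongside, without a fixed percentage denominator.
2. Keep diaries as the adherence measure common to both arms, and use them for any between-arm comparison.
3. Report agreement between diary and log in the device arm as a guide to diary error in controls. This assumes similar reporting in the two arms, which should be stated as a limitation: families using a device that logs sessions may report differently.
4. Before data are seen, state how log-based adherence will inform the progression recommendation. Whether to set a threshold, and at what level, is for the trial team; with about 20 children, any observed rate should be read with its interval.

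The cost is small but not nil. Children log on under a pseudonym of their own choice on four shared devices, so each pseudonym must be linked to a participant number, and the logs must be exported before a device moves on. Table 1, the Progression criteria section and the SAP need short wording changes. Measured adherence may also look less favourable than diary adherence.

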## Methods and analysis

### Trial design and setting

The research question is as follows: Is it feasible to conduct a multicentre randomised control trial of a physiotherapy programme using an interactive exercise trainer to improve balance in ambulant children with CP? This trial is a single-blinded; multicentre feasibility RCT with embedded qualitative study. Community paediatric physiotherapists working at Child Development Centres (CDCs) will recruit children from their caseloads. The study will be conducted between 9 February 2021 and 1 August 2022. Participants will be randomly allocated to training with the Happy Rehab device, or to the control group of usual physiotherapy care. Both groups will carry out 10 weeks training at home, the clinic or their school. The study will compare the intensity of training in different settings. Qualitative semistructured interviews with a subgroup of physiotherapists, parents and children will take place to explore their experiences of taking part; interviews will take place in the clinic or child’s home.

The research question can be framed in the following way:

P Population—Children with CP aged 4–18 years.

I Intervention—A programme of physiotherapy using the interactive training device.

C Comparison group—Usual care.

O Outcome of interest—Feasibility of the trial and intervention.

T Time—Training three times per week for 10 weeks, plus follow-up at week 10 and week 20.

The trial flow chart is shown in figure 2.

**Figure 2 F2:**
[figure not shown]
Trial flow diagram. CI, chief investigator; T, time in weeks.

### Participants

The eligibility criteria for participants are shown in box 1.

Box 1Eligibility criteriaInclusion criteriaDiagnosis of CP GMFCS I–III.Aged 4–18 years.Leg weakness (≤4/5 on the Medical Research Council (MRC) muscle strength rating scale) in at least 1one muscle group.Leg hypertonia (≥1 on the Tardieu scale fast stretch) in at least 1one muscle group.Ability to interact with a computer game using a mouse or joystick.Exclusion criteriaSelective dorsal rhizotomy or multilevel orthopaedic surgery within the last 12 months.Soft tissue surgery in lower limbs in last 6 months.Botulinum toxin injections in the lower limbs within previous 3 months.Training with the Happy Rehab in the last 4 months.

### Intervention

Four devices will be available and situated in special schools, CDCsor the child’s home. The child’s physiotherapist will be trained to set up the device targeting exercises to improve range of movement, contracture and muscle weakness. This may include active-assisted hip, knee or ankle movements within specified ranges of movement or side-to-side and forward and back weight transfer. The treating physiotherapist will personalise the exercise programme based on a standardised assessment, including a discussion with the child and their guardian about their goals and aims of any intervention.

The child will use a pseudonym of their choice to log onto the games, and to maintain confidentiality. Children will play the games within the mid-range of muscle length to begin with so that the games are difficult but achievable. This will aid motivation and adherence. After 5 weeks, the child’s physiotherapist will progress the games by requiring the muscles to work in the inner and outer ranges of movement and/or against increased resistance. Training will build up to 20 min per day, 3 days a week over a 2-week period, with progression to a 30 min programme per day, 3 days a week after 5 weeks. The child will train with supervision from by the child’s therapist, teaching assistant, parent or carer. The children will follow a series of games following a 2 min warm up of continuous passive movement. The interactive trainer records the training session (duration, games performed games outcomes) to provide a description of the parameters of training.

The control group will receive a usual care physiotherapy programme individualised for each child lasting 20–30 min.

Collaborative goal setting combined with an e-diary will allow the children and their parents/carers from both arms of the study to monitor progress over time and record their satisfaction with their exercise programme. The research team will assess fidelity through e-diaries, recording of exercise parameters via the interactive trainer and by observing ten exercise sessions and completing a fidelity checklist, to ensure the intervention follows protocol.

